### Statistical analysis

The between study group equivalence of participant characteristics and outcome measures at baseline will be compared using Chi-squared tests (dichotomous/categorical data) and t-tests (continuous data). Study hypotheses related to the confirmatory questions will be initially tested under an “intent-to-treat” model in which data are analyzed according to treatment assignment at randomization. We will then conduct “completer analyses” on those subjects completing at least two-thirds of intervention sessions. Intervention impact will be evaluated by comparing primary study outcomes between intervention and control groups across the three time points: baseline, 6 months and 12 months post-intervention. Initially, summary scores of outcomes will be stratified by participation in the intervention versus control groups and by time point, and will be compared using chi-square tests (binary or categorical outcomes), t-tests and analysis of variance (continuous outcomes). Generalized linear mixed effects models (GLMM) accounting for within-group correlation across longitudinal data will then be applied. Outcomes will be modeled as a function of group assignment and time since intervention. The association between outcomes and time will be explored visually using scatterplots and lowess smoothers. Restricted cubic splines will be added to reflect deviations from linearity.

If siblings enter the study, they will be randomized to the same intervention group to limit contamination. In this case, analyses will be adjusted to take into account intra-sibling correlation as well. Additionally, sensitivity analyses will be conducted including and excluding siblings to examine the impact on study results. Missing data will be handled as follows: 1) identify erroneous data, 2) document reason(s) for missing and erroneous data to inform model development; 3) compare demographic characteristics of those who dropped out and those who did not to compare if data is missing at random; and 3) conduct sensitivity analysis to compare inferences that are based on different plausible reasons for missingness. Navajo and Hopkins investigators will collaborate with community partners in data interpretation to assure accuracy, cultural acceptance and relevance.

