**Methods:**

*N* = 410 female adolescents ages 10–14 and their female caregivers will be enrolled in the study and randomized to the intervention or control arm. The intervention consists of the 11-session Asdzáán Be’eena’ program. The control arm consists of mailed non-monetary incentives. All participants will complete evaluations at baseline and 3 follow-up timepoints (immediate, 6 and 12 months post intervention). Evaluations include measures to assess protective factors associated with delayed sexual initiation and substance use.

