#### Control condition

The control condition consists of the delivery of four non-monetary retention items totaling <$20/dyad to the participant’s home. Retention items were selected by the community and provided as a way to continue to stay in contact with families for follow-up data collection.

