#### Discontinuing or modifying intervention

Participants will not be allowed to change groups. They will be able to stop participating at the study at any point. Study staff are trained to identify and report adverse events. In the event of an adverse event, the study staff member will call the PI and follow-up with an email detailing the event. All adverse events will be sent to the IRB according to their required schedule. The study will be reviewed by approving IRBs annually. There is no post-trial care or compensation for those who suffer harm from trial participation.

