### Retention

Participants will receive gift cards for participation in assessments ($20 per assessment time point per participant). Additionally, FHCs and IEs will do all they can to keep participants enrolled and engaged including providing transportation to study visits and snacks or meals at these visits. Participants will only be dropped from the program if they request. Outcome data will be collected from all participants regardless of their intervention completion status.

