The sample size of 410 dyads (*n* = 205 per study arm) will be sufficient to detect a 0.3 difference between study groups, with 90% power and 0.05 significance level, on the communication scale at 12 months post-intervention (estimating a mean score (SD) of 2.81(0.85) in the control group). This same sample size will be sufficient to detect an 18% between-group difference, with 80% power and 0.05 significance level, in the proportion of participants who report intention to abstain from sex at 12 months post-intervention (estimating 50% of the control group to report intention to abstain from sex at 12 months post-intervention). This sample size will also be able to detect meaningful differences in other key confirmatory research question outcomes at 12 months post-intervention. The following presents minimum detectable differences between the intervention and control groups with at least 80% power, given the assumptions listed above: 0.39 between-group difference in internalizing behaviors (estimating a mean score (SD) of 5.23 (0.99) in the control group), and 0.25 between-group difference in externalizing behaviors (estimating a mean score (SD) of 2.04 (0.63) in the control group). All estimates assume 10% attrition between enrollment and program completion and a 25% attrition rate between program completion and the 12 month follow-up time point.

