This study also has limitations. First, all outcomes are measured via self-report and/or via interview. While self-report is the most widely used methodology to assess behavior change, it is not without biases. There are also potential biases in interview administration, such as… [70]. However, steps have been taken to reduce potential biases. The IEs are highly trained in evaluation administration and human subjects research and will not deliver any part of either AB program or condition non-monetary gifts, limiting potential evaluator bias. Other methods to reduce bias include: 1) all IEs will be Native women from the local community, 2) the same IE will conduct the baseline and all follow-up assessments for each dyad, 3) all interviews will be conducted in person (vs. some in person and some via telephone/video call), and 4) the most sensitive questions focused on actual behavior and behavioral intention are conducted via self-report (not interview).

Another limitation is that the follow-up time period is only 1 year. Since adolescents are 10–14 years of age when enrolling in this program, we do not expect a large proportion of adolescents to initiate substances or have sex by the 12 month follow-up timepoint. Thus, we do not expect to have adequate power to assess impact of AB on actual behaviors. However, we will have power to assess the impact of AB on behavioral intention. Studies indicate there is a strong, positive association between intention to abstain from sex and delayed sexual initiation [71]. Further, we will assess key protective factors that are associated with delayed sexual initiation and substance use among Native and non-Native adolescents [19, 23, 71].

Third, there is potential for some contamination between control and intervention groups, as this study will be conducted in a small communities where many families know each other. To limit contamination, we will individually randomize dyads and assign siblings to the same randomization group.

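### The completer analyses condition on attendance that only the intervention arm can show, so any contrast with controls is not randomized; a complier-average estimate with stated assumptions would serve better as a supportive analysis

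*Protocol article*

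**What the plan says.** In the protocol article, Statistical analysis, the confirmatory hypotheses "will be initially tested under an “intent-to-treat” model in which data are analyzed according to treatment assignment at randomization". The same hypotheses are then examined in completer analyses "on those subjects completing at least two-thirds of intervention sessions". The section does not say with whom completers are compared, gives no adjustment for selection into completion, and does not label the analysis exploratory.

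Other sections bear on the point:
- Abstract, Methods: "The intervention consists of the 11-session" program.
- Control condition: "The control condition consists of the delivery of four non-monetary retention items". Controls have no sessions.
- Discontinuing or modifying intervention: "Participants will not be allowed to change groups".
- Retention: "Outcome data will be collected from all participants regardless of their intervention completion status".
- Discussion, limitations: "there is potential for some contamination between control and intervention groups".

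**The concern.** Completion is observed after randomization, is chosen by the family, and exists in one arm only. Read literally, the completer set contains no controls at all. Read in the only way that gives a between-arm contrast, it sets a self-selected part of one arm against the whole of the other.

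Selection on the outcome is plausible here. Table 1 lists six individual and five group lessons, so a dyad that reaches 8 must attend at least two group lessons (8 − 6 = 2) at a central location, caregiver and girl together. The relationship outcomes are communication, quality time, warmth and monitoring. A pair willing to turn up together that often may well score higher on these without any program. If so, the completer result would tend to look better than the ITT result even if the program did nothing, and could be read as supporting efficacy.

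**Working it through.** The article gives no figure for the completer analysis, so there is none to reproduce. The size below is illustrative.

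**Inputs from the article (Randomization and sample size)**
- 205 dyads per arm; attrition 10%, then 25%. Retained: 205 × 0.90 × 0.75 = 138 per arm.
- Communication scale: SD 0.85, design difference 0.3.
- Threshold: 2/3 × 11 = 7.33, so at least 8 sessions.

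**Assumed, because the article is silent**
- c, the share of intervention dyads that complete: 60% to 90%.
- ρ, the correlation between a normal latent propensity to complete and the 12-month score: 0.1 to 0.3.

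**Step 1: bias with no program effect, unadjusted 12-month comparison**

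Bias = ρ × φ(z_c)/c × SD, where φ(z_c) is the normal density at the completion cut-off. Standard error = SD × √(1/(138c) + 1/138).

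For c = 0.7 and ρ = 0.2: bias = 0.2 × 0.348/0.7 × 0.85 = 0.084, which is 28% of 0.3. The standard error is 0.113, and the two-sided 5% test rejects 11.6% of the time.

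| Completion | Bias, ρ = 0.1 / 0.2 / 0.3 | Rejection rate, ρ = 0.1 / 0.2 / 0.3 |
|---|---|---|
| 60% | 0.055 / 0.109 / 0.164 | 7.5% / 15.3% / 28.5% |
| 70% | 0.042 / 0.084 / 0.127 | 6.6% / 11.6% / 20.2% |
| 80% | 0.030 / 0.059 / 0.089 | 5.9% / 8.5% / 13.0% |
| 90% | 0.017 / 0.033 / 0.050 | 5.3% / 6.1% / 7.6% |

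**Step 2: a second parameterization**

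Let g be the untreated difference, in SD units, between dyads who would and would not complete. Bias = (1 − c) × g × SD. For c from 0.9 to 0.6 and g from 0.2 to 0.5 this runs from 0.1 × 0.2 × 0.85 = 0.017 to 0.4 × 0.5 × 0.85 = 0.170. In simulation under no effect (138 per arm, 6,000 runs, c = 0.6 to 0.8, g = 0.3 or 0.5), the completer contrast rejected in 8% to 31% of runs. ITT stayed at about 5%, and the instrumental-variable (IV) estimate was centred on zero.

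**Step 3: effect of baseline adjustment**

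Suppose completion relates equally to baseline and 12-month scores, and these correlate at k (assumed 0.5 to 0.7). The bias is multiplied by 1 − k and the standard error by √(1 − k²). For c = 0.7 and ρ = 0.2, the bias falls from 0.084 to 0.042 (k = 0.5) or 0.025 (k = 0.7), and rejection from 11.6% to 7.2% or 6.1%.

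**Step 4: the IV alternative**

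Let d be the effect in completers and f the fraction of d that partial attenders receive. ITT = c·d + (1 − c)·f·d, and IV = ITT/c.
- d = 0.3, f = 0: IV = 0.30. Completers against all controls (g = 0.3) would give 0.35 at c = 0.8 and 0.40 at c = 0.6.
- d = 0.3, f = 0.5, c = 0.7: ITT = 0.21 + 0.045 = 0.255, and IV = 0.255/0.7 = 0.36.
- d = 0.3, f = 0.5, c = 0.6: IV = 0.24/0.6 = 0.40. Its bias of 0.10 equals the completer bias at g = 0.3 (0.4 × 0.3 × 0.85 = 0.10).
- Precision: the ITT standard error, 0.85 × √(2/138) = 0.102, becomes about 0.102/0.7 = 0.146 at c = 0.7. The IV test is in effect the ITT test.

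**The case against.** The strongest reply is that the confirmatory test keeps randomization. ITT comes first, and a follow-on completer analysis is common practice. A reader might infer that the completer result is a second main efficacy result, or that the trial's conclusion is compromised. The article supports neither: it ties no success claim to completers and does not let them override ITT.

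The comparator is also inferred, and a condensed article may leave comparator, adjustment and labelling to the analysis plan. That stands for those details. It does not remove the point, because the article itself fixes the population and the threshold, and no choice of control comparator makes that population a randomized group.

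The illustrated sizes are for an unadjusted comparison, whereas the plan also fits longitudinal models that include baseline. Step 3 shows that adjustment can cut the bias by half or more. However, the article also plans unadjusted comparisons at each time point and does not spell out a group-by-time term. High attendance is possible too, and at 90% completion the bias is small.

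A reader might also infer that an IV estimate answers the same question free of bias. That is too strong. At the 8-of-11 cut-off it assumes that 1 to 7 lessons have no effect, which is hard to defend for a curriculum that teaches skills lesson by lesson. It also assumes no spillover to controls, while the Discussion acknowledges possible contamination.

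The fractional threshold is not a defect: at least two-thirds of 11 resolves to 8.

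**Conclusion.** The point holds as a weakness of the follow-on analysis only. Followed as written, the completer analysis either contains no controls or makes a non-randomized contrast that is biased whenever attendance is related to the outcome. If more engaged families do better anyway, the bias favours the program.

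The size rests on assumed completion and correlation. Over 60% to 90% completion and correlations of 0.1 to 0.3, an unadjusted comparison is off by 0.017 to 0.164 points on the communication scale and rejects a true null 5.3% to 28.5% of the time. At 90% completion or with baseline adjustment the effect is much smaller. The ITT result is not affected.

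A complier-average estimate is the better supportive analysis. It uses the randomized comparison, and the data should exist because outcomes are collected whatever the attendance and group changes are barred. It is better only if its assumptions are stated and tested.

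**What to change.** 1. State that ITT is the only confirmatory analysis.
2. Replace the completer analysis with a supportive complier-average estimate: two-stage least squares with randomized arm as instrument, adjusted for baseline value and site. Preferably make the number of sessions attended the exposure, and use the 8-of-11 cut-off as a sensitivity analysis.
3. State the assumptions:
   - assignment acts only through attendance (at the 8-of-11 cut-off, partial attendance has no effect; otherwise the estimate overstates, as in Step 4);
   - for the sessions version, the form of the relation between sessions and outcome;
   - no spillover to controls;
   - how missing 12-month outcomes are handled, given the assumed loss of 32.5% (1 − 0.90 × 0.75).
4. Keep the planned allowance for siblings in the standard errors. Any adjustment for program cohorts must allow for cohorts existing only in the intervention arm.
5. If a completer contrast is kept, name its comparator and label it exploratory and non-randomized.

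The cost is analysis wording, with no new data. The IV interval is wider than the completer interval, and there is no gain in power over ITT.

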### Outcomes

Assessments will be administered at baseline, immediately following program completion and 6- and 12-months following program completion (see Table 2). Data will be collected in participants’ homes or another private location via a tablet using Research Electronic Data Capture (REDCap). Caregivers will complete all assessments via self-report. Adolescents will complete portions of the outcome assessment asking about sexual and substance use behaviors via self-report. All other portions will be be completed via interview. Participants will be given $20 after completion of the baseline, immediate, six and twelve month post intervention assessments. All measure items were previously piloted with adolescent and caregivers from the community to assess comprehension, language, and cultural relevance. Edits were made accordingly and pilot participants were not eligible for the RCT.

**Table 2 Tab2:** Study Evaluation: constructs measured, method of administration and timepoint administered

Construct Measured	Completed by	Method ofadministration	Timepoint Administered			
			Baseline	Immediate Post	6 month post	12 month post

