### Randomization and sample size

This study will use a 1:1 randomized controlled trial design; the unit of randomization will be the individual dyad. Unique participant identification numbers will be used to randomize individual dyads to one of two study groups: intervention or control. Stratified block randomization, using random block size will be used to ensure a 1:1 allocation of study conditions across the two study sites. The sequence will be generated by the program evaluation via STATA and will not be shared with study staff who enroll participants.. Independent Evaluators will enroll participants and reveal study group after the participants complete the baseline assessment. The study assignments are sequentially numbers in sealed envelopes that are only opened at the time of randomization. No blinding will occur.

Sample size and statistical power estimates are predicated on 2 primary hypotheses: 1) that those randomized to the AB intervention will have improved parent-adolescent communication compared to the control group, and 2), that those randomized to the AB intervention group will have a higher proportion of participants who report they intend to abstain from sex.

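### The impact analysis names three of the four waves collected, leaving immediate-post scores unused for most expected dropouts, and a demographic comparison cannot show that data are missing at random

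*Protocol article*

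**What the plan says.** The Outcomes section schedules four waves: "Assessments will be administered at baseline, immediately following program completion and 6- and 12-months following program completion". Table 2 marks both primary constructs, the caregiver-adolescent relationship and intentions about sexual activity, at all four.

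The Statistical analysis section evaluates impact by "comparing primary study outcomes between intervention and control groups across the three time points: baseline, 6 months and 12 months post-intervention" and gives no reason for leaving out the immediate-post wave. It then applies generalized linear mixed models with group and time since intervention as predictors. That sentence does not list waves itself.

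The same section handles missing data in four steps: find erroneous values, document reasons for missingness, "compare demographic characteristics of those who dropped out and those who did not to compare if data is missing at random", and run a sensitivity analysis over different plausible reasons for missingness.

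Randomization and sample size assumes 10% attrition to program completion and a further 25% from there to 12 months. The hypotheses in the Objectives section are at 6 and 12 months.

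**The concern.** Two linked weaknesses are in the text itself.

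**The unused wave.** A likelihood-based mixed model protects against dropout only to the extent that dropout is explained by what is in the model. Suppose the chance of leaving depends on how a dyad scored at program end. With that score in the model, the loss is missing at random. Without it, the same loss is in general not missing at random given what the model sees. For a dyad lost between program end and 6 months, the immediate-post score is the only outcome observed after baseline.

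**The check.** Whether data are missing at random or not at random turns on values nobody observed, so no comparison of observed characteristics can decide it. A demographic difference between dropouts and completers is evidence against missing completely at random. The absence of one is not evidence for missing at random. The comparison as worded also ignores earlier outcome scores, which are the observed variables that matter most for the model.

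At stake is the 12-month contrast on which the trial is sized, in an unblinded trial where one arm receives eleven lessons and the other four small mailed or delivered items. Dropout related to outcome in different ways by arm is plausible there, though the protocol does not show that it will happen.

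**Working it through.** **1. Reproduce the plan's figure, to confirm how attrition is combined.** Inputs from Randomization and sample size: "The sample size of 410 dyads" (205 per arm), difference 0.3, SD 0.85, 90% power, significance level 0.05.

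- n per arm = 2 × SD² × (z₁ + z₂)² / difference².
- One-sided 0.05: 2 × 0.7225 × (1.645 + 1.282)² / 0.09 = 137.5, so 138.
- Retention: 0.90 × 0.75 = 0.675. Then 138 / 0.675 = 204.4, so 205 per arm and 410 in all.

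The stated total is reproduced with multiplicative attrition and a one-sided test. A two-sided test would need 169 per arm, or 502 in all after inflation. Sidedness is a separate matter and does not affect this point.

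**2. Who is lost, and who has the unused score.**

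| Quantity | Arithmetic | Dyads |
|---|---|---|
| Lost before program completion | 410 × 0.10 | 41 |
| Reach program completion | 410 × 0.90 | 369 |
| Lost from completion to 12 months | 369 × 0.25 | about 92 |
| Lost in all by 12 months | 410 × 0.325 | about 133 |

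If the first 10% leave before the immediate-post visit, 92 / 133 = 69% of those lost have an immediate-post score. The protocol does not say how the 92 divide between loss before and after 6 months.

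**3. Size of the bias (illustration; these assumptions are not in the protocol).** Communication scale, SD 0.85, true difference 0.30 at every post-baseline wave. All pairs of waves have the same correlation, 0.3 to 0.7. 10% are lost at random before immediate-post and 25% after it. Low immediate-post scores raise the log-odds of dropout by 0.6 or 1.2 per SD. The 12-month difference was estimated in very large samples, by successive regression within arm (equivalent to a likelihood model with unrestricted covariance). The share of these dropouts already missing at 6 months was set at none, half or all.

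Score-dependent dropout in the intervention arm only, random in the control arm:

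| Correlation | Log-odds per SD | Completers only | Three waves | Four waves |
|---|---|---|---|---|
| 0.3 | 0.6 | 0.34 | 0.32 to 0.33 | 0.30 |
| 0.3 | 1.2 | 0.36 | 0.34 | 0.30 |
| 0.5 | 0.6 | 0.36 | 0.32 to 0.33 | 0.30 |
| 0.5 | 1.2 | 0.40 | 0.34 to 0.36 | 0.30 |
| 0.7 | 0.6 | 0.39 | 0.32 to 0.33 | 0.30 |
| 0.7 | 1.2 | 0.44 | 0.33 to 0.35 | 0.30 |

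The ranges run over the share missing at 6 months, with the larger bias when all are. The three-wave bias is therefore about 0.02 to 0.06.

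Same mechanism in both arms (all dropouts missing at 6 months): completers, three waves and four waves all give 0.30.

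**4. Cost of the fourth wave.** When dropout is unrelated to outcome, at correlation 0.5, the standard error of the 12-month contrast is 0.087 to 0.088 whether or not the wave is included.

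**The case against.** The strongest reply has four parts.

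- **The three waves match the hypotheses.** Comparisons are wanted at 6 and 12 months, so not testing at immediate-post is consistent. This stands. It explains the tests but not the exclusion of the wave from the model.
- **The model sentence lists no waves,** so the fourth may be intended, and model detail may sit in an analysis plan not shown. This is fair. However, the sentence that defines how impact is evaluated counts and names three time points, and the model sentence follows in the same account. If four waves are meant, the text needs correcting.
- **Demographics are not the only safeguard.** A reader might infer that the plan rests its missing-data case on that comparison. It does not: reasons for missingness are documented and a sensitivity analysis over plausible reasons is planned. The particular method for that analysis can properly be left to the analysis plan. What remains is the stated purpose of the comparison, which it cannot serve.
- **The bias needs a particular scenario.** This also stands. It arises when dropout depends on the score differently by arm, and even then it is below one standard error.

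Two stronger readings are not supported. One is that the immediate-post score is the best predictor of 12-month outcomes for everyone lost after program end. Dyads lost after 6 months have a later score already in the three-wave model, and the protocol gives no correlations. The other is that the result will be inflated to the completers-only figures. Those describe unadjusted comparisons such as the t-tests, which the plan runs first and follows with the mixed model.

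**Conclusion.** The point holds as a modest, nearly free improvement plus a wording correction. The documents establish that four waves are collected and three are named for the impact analysis, that 32.5% loss is planned for, and that a demographic comparison is given a purpose it cannot serve. The count of about 92 of 133 rests on the first 10% leaving before the immediate-post visit. The bias of about 0.02 to 0.06 on 0.30 rests on assumed correlations and on score-dependent dropout confined to the intervention arm; dropout of the opposite pattern would reverse its sign. With a common mechanism it is about zero. The size was worked only for the continuous communication scale. For the binary intention outcome the reasoning carries over, but no figure is offered. Nothing here shows that the planned analysis will be materially wrong.

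**What to change.** 1. In Statistical analysis, name immediate-post as a further occasion in the mixed model, with time as categorical and a flexible covariance. Keep the 6- and 12-month contrasts as the tests, so that no hypothesis is added.
2. Reword the comparison of dropouts and completers as descriptive, and add earlier outcome scores to the demographics, by arm.
3. State as an assumption that outcomes are missing at random given arm, site, baseline and earlier outcomes, and say that the sensitivity analysis already planned examines departures from it.

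The cost is a few sentences and one set of model runs. No new data or visits are needed, the sample size is unchanged, and essentially no precision is lost.

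### No stated between-arm analysis uses the girl's own baseline score as a covariate or constrains baseline means, which gives up precision the trial has already paid for

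*Protocol article*

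**What the plan says.** The Outcomes section states: "Assessments will be administered at baseline, immediately following program completion and 6- and 12-months following program completion". The heading rows of Table 2 for the caregiver-adolescent relationship and for sexual intentions mark all four time points. The Randomization and sample size section has group assignment revealed only after the baseline assessment, so the baseline score is a clean pre-allocation variable.

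The Statistical analysis section gives baseline scores two uses: a test of equivalence between the arms at baseline, and a place as one of three time points (baseline, 6 and 12 months) over which the arms are compared. The comparison has two steps. First, summary scores by arm and time point "will be compared using chi-square tests (binary or categorical outcomes), t-tests and analysis of variance (continuous outcomes". Second, a generalized linear mixed model (GLMM) that allows for correlation across the longitudinal data is applied: "Outcomes will be modeled as a function of group assignment and time since intervention". No baseline covariate and no common-baseline constraint is named, and neither step is called the confirmatory test.

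The sample size is set on the unadjusted comparison. Its stated aim is: "detect a 0.3 difference between study groups, with 90% power and 0.05 significance level, on the communication scale at 12 months post-intervention". The controls are taken to have an SD of 0.85 around a mean of 2.81.

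**The concern.** A scale's own baseline value is usually among the strongest predictors of the same scale a year later. If the correlation is ρ, using baseline as a covariate multiplies the variance of the arm difference by 1 − ρ². A t-test at 12 months gets none of this. A difference in change from baseline has variance factor 2(1 − ρ), which equals the raw variance at ρ = 0.5 and exceeds it below that. Putting baseline into the GLMM as one more response therefore does not by itself deliver the gain.

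At stake are the power and interval width for the communication scale, which set the sample size, in a trial that expects to lose about a third of its dyads by 12 months. Naming the adjustment in advance also removes a later choice between adjusted and unadjusted results.

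**Working it through.** **Inputs from Randomization and sample size.** 205 dyads per arm, difference 0.30, SD 0.85, significance level 0.05 (sidedness not stated), attrition 10% and then 25%. Retained at 12 months: 205 × 0.90 × 0.75 = 138.4, taken as 138 per arm.

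**Assumed.** The baseline to 12-month correlation ρ, which the protocol does not give; 0.3 to 0.6 is shown. Normal approximation throughout.

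**1. The protocol's own figure.** SE = 0.85 × √(2/138) = 0.1023, so 0.30/0.1023 = 2.932.
- One-sided 0.05: Φ(2.932 − 1.645) = 90.1%. Required n = 2 × (0.85/0.30)² × (1.645 + 1.282)² = 137.5, so 138 retained, and 138/0.675 = 204.4, so 205 per arm. This reproduces the stated 90% and the sample size.
- Two-sided 0.05: Φ(2.932 − 1.960) = 83.4%. For 90%, 169 retained or 251 enrolled per arm would be needed.

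**2. Baseline as a covariate against the 12-month t-test.** SE becomes 0.1023 × √(1 − ρ²). At ρ = 0.5 this is 0.1023 × 0.866 = 0.0886, and 0.30/0.0886 = 3.385. Two-sided power is Φ(3.385 − 1.960) = 92.3%; one-sided it is Φ(3.385 − 1.645) = 95.9%.

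| ρ | Two-sided (t-test 83.4%) | Gain, points | One-sided (t-test 90.1%) | Gain, points |
|---|---|---|---|---|
| 0.3 | 86.7% | 3.3 | 92.3% | 2.2 |
| 0.4 | 89.2% | 5.8 | 94.0% | 3.9 |
| 0.5 | 92.3% | 8.9 | 95.9% | 5.8 |
| 0.6 | 95.6% | 12.1 | 97.8% | 7.7 |

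**3. Against the GLMM.** Suppose the GLMM has a group-by-time term and an unconstrained baseline, and the test is the 12-month change-from-baseline contrast. With 138 complete cases per arm, the SE is 0.1023 × √(2(1 − ρ)). Two-sided power is 69.8% at ρ = 0.3 and 83.4% at ρ = 0.5.

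A likelihood-based model also uses girls who drop out. For this, generalized least squares was run with an exchangeable correlation and 205, 161 and 138 girls per arm at baseline, 6 and 12 months. The 161 is an assumption, midway between 205 × 0.90 = 184.5 and 138.4. Two-sided power at 12 months:

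| ρ | Unconstrained group-by-time | Baseline means constrained equal | Gain, points |
|---|---|---|---|
| 0.3 | 75.2% | 87.0% | 11.8 |
| 0.5 | 86.9% | 92.7% | 5.8 |
| 0.6 | 92.8% | 95.9% | 3.1 |

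The two gains run in opposite directions. As ρ rises, the gain over the t-test grows and the gain over the change contrast shrinks.

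**4. Intention to abstain.** For 50% against 68% with 138 per arm, unadjusted two-sided power is 86% to 87%, depending on whether the variance is pooled. The stated target is 80%.

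**The case against.** The t-tests and chi-square tests are only the first step. The GLMM that follows includes baseline among its time points and models within-person correlation, and a common-baseline model is compatible with the wording. An article may leave covariates and mean structure to an analysis plan that is not shown. Unadjusted comparison of randomized arms is unbiased, and sizing on the raw SD is conservative.

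Much of this stands and limits the claim. It does not remove it. The article does not merely stay silent: it names the tests, the model terms and the role of baseline as a compared time point, and under those terms the gain is not secured. Modelling the correlation is not the same as adjusting for baseline, as step 3 shows.

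Four stronger readings are tempting and are not supported:
- **A loss of 9 points whatever analysis is used.** That figure belongs to the two-sided t-test at ρ = 0.5. It passes over the GLMM, against which the gain at that ρ is about 6 points.
- **A missed power target.** The 83% follows only if testing is two-sided. The protocol does not state sidedness, and the one-sided calculation meets the stated 90%.
- **Bias.** Chance baseline imbalance stays in the unadjusted estimate, but randomization keeps that estimate unbiased.
- **A GLMM with no interaction.** Taken literally, group and time main effects with baseline as a response would dilute the group coefficient to 0.20, with 66.8% two-sided power at ρ = 0.5 (138 complete cases per arm, effect 0.30 at both 6 and 12 months). The text does not exclude an interaction, so this point does not rest on that reading.

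**Conclusion.** The point holds as a nearly free improvement in efficiency. As stated, the plan does not use the pre-allocation baseline score as a covariate or constrain baseline means. For communication at 12 months and ρ = 0.5, the gain over the t-test is 9 points two-sided (83% to 92%) or 6 points one-sided (90% to 96%). Across ρ of 0.3 to 0.6, the two-sided gain is about 3 to 12 points over the t-test. Over an unconstrained group-by-time GLMM that uses dropouts, it falls from about 12 points at ρ = 0.3 to 3 at ρ = 0.6.

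These sizes rest on an assumed ρ, on an unstated sidedness and, for the GLMM figures, on an exchangeable correlation and the assumed 161 per arm at 6 months. For intention to abstain the benefit is precision only. An analysis plan that is not shown may already specify the adjustment.

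**What to change.** In the Statistical analysis section, make the confirmatory comparison at 6 and 12 months baseline-adjusted, in one of two ways:
- enter the girl's own baseline score as a covariate, with only post-baseline visits as outcomes; or
- fit a longitudinal model with a group-by-time structure in which baseline means are constrained equal across arms.

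For intention to abstain, include the baseline response in the binary model and report a standardized risk difference, so that the estimate is on the same scale as the 18-point difference used for sample size. Label the unadjusted t-tests, ANOVA and chi-square tests as descriptive.

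The cost is a few sentences, with no new data, visits or participants. Missing baseline items need a simple rule, such as mean imputation of the baseline covariate, and the binary outcome needs a standardization step.
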